## Abstract

**Background:**

Diabetes is an important health burden in Indonesia. However, diabetes management and treatment remain poor, with most people with diabetes in Indonesia not achieving the recommended blood glucose levels. Peer education may have particular potential in low-income settings in complementing diabetes care without being a large additional strain on the health system.

**Methods/design:**

This cluster randomized controlled trial aims to identify the effect of the implementation of peer education for patients with type 2 diabetes on diabetes-related outcomes in Aceh, Indonesia, which will complement the diabetes treatment provided at primary-care health posts (*puskesmas*). Altogether, 29 *puskesmas* were recruited in Banda Aceh and Aceh Besar, each of which was randomly assigned to either the control or the intervention group. Then, 534 people with diabetes were identified and recruited through their respective *puskesmas*. The intervention consists of up to two peer education groups per *puskesmas*, which are led by previously trained people with diabetes. Peer education sessions are held every month for 18 months, with follow-up data being collected 9 and 18 months after the first peer education session.

The main objective is to improve diabetes management and the health behavior of participants receiving peer education to reduce their average blood glucose levels as measured by glycated hemoglobin (HbA1c) levels. Secondary outcomes are the effects of peer education on lipid levels, waist circumference, blood pressure, quality of life, treatment adherence, diabetes knowledge, physical activity, and dietary diversity. Data sources for the measurement of outcomes include patient and health facility surveys and biomarker measurements. An economic evaluation will be conducted to assess the cost-effectiveness of the intervention.

**Discussion:**

This trial will contribute to the evidence on the effectiveness and cost-effectiveness of peer education in improving diabetes management in a low-income setting in Indonesia and in other comparable contexts.

**Trial registration:**

ISRCTN registry, ISRCTN68253014. Registered on 18 February 2019.

**Electronic supplementary material:**

The online version of this article (10.1186/s13063-019-3656-1) contains supplementary material, which is available to authorized users.

## Background

Public health systems in low- and middle-income countries are overburdened with the demands of delivering care to those with communicable and non-communicable diseases. People with the latter in particular often require long-term monitoring and support to achieve good health [1]. For diabetes, inadequate care or no access to care can lead to high rates of uncontrolled diabetes and complications. It is unclear, however, how better care can be provided in an environment with few resources, as is the case in low- and middle-income countries.

In Indonesia, diabetes has become one of the main contributors to the burden of disease, surpassing many communicable diseases, especially among adults [2]. However, diabetes treatment at the main public primary-care facilities, *puskesmas*, remains poor, which is partly due to the limited knowledge of health-care professionals about diabetes [2, 3]. Consequently, recent studies on diabetes in Indonesia indicate poor levels of control, with around 70% of patients having glycated hemoglobin (HbA1c) levels above 7% [4].

A potential way to complement the diabetes care available in Indonesia is the use of peer education, in which highly motivated and trained diabetes patients educate and support other patients with diabetes to manage the disease in daily life in a culturally appropriate way. Due to the need for patients to deal with their diabetes every day, and the potential of lifestyle changes and preventative behavior to prevent major diabetes complications, empowering patients by increasing their knowledge of diabetes care could theoretically yield positive results. Peer education focuses and relies on people with diabetes, rather than medical professionals, to improve diabetes care. Therefore, it may be less resource intensive than traditional approaches and particularly attractive in environments where access to and the quality of diabetes health care are very limited [5].

Several randomized controlled trials have been conducted in recent years to test the efficacy of peer education in improving diabetes outcomes in high- and in some low- and middle-income countries. Two systematic reviews have indicated that peer education overall can lead to statistically significant reductions in HbA1c levels [5, 6]. It appears that it is especially effective for some sub-groups of diabetes patients, such as those with relatively uncontrolled diabetes [5] and minorities [6]. Because most of the trials reviewed took place in high-income countries, these results may not be directly applicable to relatively poorer countries. The two studies that evaluated the effects of peer education in a middle-income country (China and Argentina), took place in an urban environment (La Plata, Argentina [7] and Hong Kong [8]).

Hence, there is a lack of evidence on the causal effect of peer education in low- and middle-income countries, in particular on its adaptability to non-urban environments where diabetes care mainly happens at the primary-care level.

Our study results may, therefore, play an important part in advancing the knowledge base on the treatment of diabetes in low- and middle-income countries. In particular, it may provide evidence of its effectiveness in a setting that consists of both urban and relatively remote rural areas, and where traditional beliefs around diabetes and the use of alternative medicines are still relatively common [4].

Moreover, our study will look at the effectiveness of peer education over a relatively long time of 18 months. It further aims not only to look at HbA1c, but also at changes in lipid levels as well as blood pressure and waist circumference, given their role as risk factors for diabetes-related complications. Because peer education relies on the ability of peer educators to train their peers and the peers’ ability to use this information to change their behavior, we will also assess if the personal characteristics of study participants can mediate the success of the intervention. In particular, we want to investigate the role of time and risk preferences, which may mediate the ability of participant to prioritize behavior change today to prevent diabetes complications in the future. Finally, our study will provide estimates of the cost-effectiveness of peer education in a low-income context of a developing country. This will add further evidence about the viability of peer education in health systems of low- and middle-income countries in terms of its financial costs and effectiveness.

## Methods/design

### Study setting

In Indonesia, most people with diabetes receive their regular diabetes treatment at the primary-care level at public health posts called *puskesmas*. These are government-mandated primary-care providers and the first point of contact for people seeking care in the public health system in Indonesia. Each *puskesmas* normally serves one sub-district, which has a population of 30,000 to 50,000. The main role of *puskesmas* is the delivery of primary outpatient care, but they are also used to promote and realize public health measures such as immunization, nutrition education and health information campaigns. About one-third of *puskesmas* in Indonesia provide basic inpatient care for emergency obstetric and neonatal care. Outpatient care efforts have mainly focused on communicable diseases, so that many *puskesmas*, especially in rural areas, provide a low quality of diabetes services [2]. This is characterized by a limited capacity to detect diabetes via diagnostic tests, and to treat and manage diabetes and its complications. Diabetes care is mainly limited to the use of medication to control the disease, and mostly disregards patient education on topics such as diet or exercise [2, 3]. The diabetes burden in Aceh is mostly unknown, but judging from national data, substantial [2]. This study is taking place at *puskesmas* in the districts Banda Aceh and Aceh Besar in the north of Sumatra, with Banda Aceh consisting of mostly urban areas and Aceh Besar of rural areas.

### Study design

The study is a cluster randomized controlled trial with a parallel group design, with the clusters consisting of *puskesmas* from Banda Aceh and Aceh Besar Regency.^1^ Peer education groups were randomly established in 50% of *puskesmas* after they joined the study and baseline data collection had been terminated. This study design allows us to establish two groups of participants (treatment and control group) so that we can causally identify the effect of the peer education on the primary and secondary outcomes. Blinding was possible at baseline, which preceded the allocation of clusters into treatment and control groups. However, after the randomization and allocation, the blinding of the treatment allocation of participants, project managers, and investigators is no longer possible. For the duration of the study, the control group will not receive any intervention beyond being informed about their blood test results. The Standard Protocol Items: Recommendations for Interventional Trials (SPIRIT) checklist is provided as an Additional file 1.

### Intervention: peer education

Peer support has been defined as “support from a person who possesses experiential knowledge of a specific behavior or stressor and similar characteristics as the target population” [9]. It has been shown to help reduce or prevent problematic health behaviors and alleviate vascular disease, HIV, and Parkinson’s disease among others [5]. The appeal of peer support is its ability to create nonhierarchical reciprocal relationships through the sharing of similar life experiences between the peer educator and the peers. Additionally, because peer education relies on non-professionals to improve the health outcomes of patients, it may be significantly less resource intensive than trying to achieve the same effects with professional health workers.

The intervention was designed in cooperation with the local expert team as well as experts experienced with the implementation of peer education in a low-income context in Mali [10]. Furthermore, qualitative interviews and focus group discussions with nurses working with diabetes patients at *puskesmas* informed the intervention design, in particular regarding practicable ways to train peer educators and to provide them with the means to transfer their knowledge successfully to their peer groups.

### Training of peer educators

Selected peer educators will receive training before and after the start of the implementation. A 2-day intensive training session by local physicians on diabetes and nutrition was carried out at the beginning of April 2019 before the start of the peer education sessions. It provided general information about diabetes as a disease, its risks, and the ways to treat it. This initial information session will be followed up by monthly half-day training sessions for the peer educators until the end of the study. These training sessions for peer educators will be led by two specially trained nurses, who, prior to each training session, will be educated by a member of the research team on the specific topic to be discussed. The topics and structure of the peer educator training sessions will be guided by the peer leader manual published by the International Diabetes Federation [11]. The goals of these additional education sessions [1] are to distribute the burden of training sessions for peer educators over a longer period of time [2], to maintain the motivation and commitment of peer educators over time [3], and to use feedback from the peer educators after their peer education sessions to adapt the training to the needs of the peer educators and their peers.

### Use of peer education

Depending on the number of patients recruited per *puskesmas* and the number of potential peer educators, one or two peer educators will be selected per *puskesmas*, to limit the group size to 13 participants. Peer education sessions are planned to be held once a month for 18 months. They will be conducted by the peer educator only, without the presence of a trained nurse or a member of the research staff, to avoid any potential changes in the behavior of the peer educator or the patients. To preserve some flexibility in how peer educators conduct the peer education sessions and react to the needs of the group, we will refrain from closely monitoring each session. Rather, we will use feedback from the peer educators about the sessions to determine if they are successful in discussing the planned topics.

### Research questions

The specific research questions are:
Will HbA1c levels decrease in patients who take part in peer education groups and if so, by how much?What effect will peer education have on lipid levels, waist circumference, blood pressure, and quality of life?What effect will peer education have on health and self-care behavior of participants in the intervention group?Is the intervention cost-effectiveness?What are important mediators for the effectiveness of peer education?

### Outcome measures

The primary outcome is the change in HbA1c levels from baseline to the final assessment. HbA1c will be collected at baseline, midline and the final assessment using point-of-care testing devices allowing for the immediate measurement of HbA1c levels. Secondary outcomes are:
changes in lipids (total cholesterol, high-density lipoprotein, and triglycerides) collected using point-of-care testing devices at baseline, during the trial, and at the final assessmentblood pressurewaist circumferencediabetes knowledgemedication adherence (five-item Medication Adherence Scale, MARS-5 [12])diabetes distress (Diabetes Distress Scale 2 [13])healthy behaviors, such as smoking status and number of cigarettes per day, and physical activity levels (WHO global physical activity questionnaire [14])dietary diversity (dietary diversity questionnaire published by the Food and Agriculture Organization of the U.N. [15])

Finally, to assess the cost-effectiveness of the intervention, changes in health-care costs and changes in quality-adjusted life years (based on EQ-5D-3 L questionnaire [16]) will be used to calculate the incremental cost-effectiveness ratio of the intervention [16].

Regarding potential mediators, we specifically focus on the behavioral characteristics of the participants. In particular, we measure risk and time preferences as well as trust in other people using unincentivised questions. We also use the Collective Self-Esteem Scale, which measures the ability of participants to function in and identify with social groups [17], and the 13-item Self-Control Scale [18].

### Study duration

A qualitative study to inform the intervention was carried out in May and June 2018. As shown in the SPIRIT figure (Fig. 1), recruitment occurred in February and March 2019. Baseline data were collected in April 2019, including primary and secondary outcome variables, for all participating patients. The intensive training sessions of the selected peer educators took place in April 2019 and the peer groups were established in July 2019. The first follow-up data will be collected in April 2020, including primary and secondary outcome variables. This will be followed by an analysis of the preliminary results. The final assessment will be conducted in January 2021, including primary and secondary outcome variables. This will be followed by an analysis of the results and the establishment of peer support groups in the control group if the intervention proves to be effective.

**Fig. 1 Fig1:**
[figure not shown]
Schedule of enrolment, intervention, and assessments. HbA1c glycated hemoglobin

### Number of participants and power calculation

The study aimed to include patients from all *puskesmas* in Banda Aceh and Aceh Besar.^2^ Power calculations indicated that with 680 participants in 34 clusters, an assumed intra-cluster correlation of HbA1c of 0.37, and a pooled standard deviation of HbA1c of 1.25, we would have 80% power to detect a difference of 0.5 in mean HbA1c using a significance level of *p* = 0.05 and 90% power to detect a difference of 0.686 using a significance level of *p* = 0.01. We chose a difference of 0.5 in mean HbA1c, as this has been determined as a clinically meaningful threshold [19]. At the end of the recruitment phase, we had been able to recruit 534 participants from 31 *puskesmas*. However, two *puskesmas* could not be used as separate cluster units since their low recruitment numbers prevented the formation of a peer education group. We decided to assign the participants from these *puskesmas* to the geographically closest *puskesmas*. This reduced the number of clusters from 31 to 29, which gives 80% power to detect a difference of 0.57 in mean HbA1c using a significance level of *p* = 0.05 and 90% power to detect a difference of 0.78 using a significance level of *p* = 0.01.

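### The stated power does not follow from the stated inputs: ICC 0.37 and SD 1.25 give about 45% power for 0.5 as planned and about 49% for 0.57 as recruited, not 80%

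*Protocol article*

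**What the plan says.** The section on number of participants and power calculation gives a full set of inputs and the results attributed to them.

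- Planned size: "Power calculations indicated that with 680 participants in 34 clusters".
- Variance inputs and planned result: "an assumed intra-cluster correlation of HbA1c of 0.37, and a pooled standard deviation of HbA1c of 1.25, we would have 80% power" for a difference of 0.5 at 0.05, and 90% power for 0.686 at 0.01.
- Recruited result: 534 participants and, after two small health posts were merged with neighbours, 29 clusters, "which gives 80% power to detect a difference of 0.57 in mean HbA1c using a significance level of" 0.05, and 90% power for 0.78 at 0.01.

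The same section names 0.5 as the clinically meaningful difference. It gives no baseline correlation, covariate gain, cluster-size variation or sidedness. Under Study design, half of the clusters go to each arm. Under Outcome measures, "The primary outcome is the change in HbA1c levels from baseline to the final assessment".

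**The concern.** An ICC of 0.37 is large. With about 20 people per cluster it multiplies the variance roughly eightfold, and a trial with 17 clusters per arm and an SD of 1.25 cannot then be expected to detect 0.5 with 80% power. The ICC and SD are also described as those of HbA1c and the target as a difference in mean HbA1c, whereas the primary outcome is a change. The paragraph does not say how the one was turned into the other.

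The consequence lies in reading the result. The protocol makes peer support for the control group, and wider implementation, conditional on the intervention proving effective. If readers believe the trial had 80% power for an effect near 0.5 when it had much less, a non-significant result could be taken as evidence that peer education does not work.

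**Working it through.** **Inputs.** From the power paragraph: 680 participants in 34 clusters (20 per cluster); 534 participants in 29 clusters (mean 18.41); ICC 0.37; SD 1.25. From Study design: equal allocation of clusters, hence 17/17 as planned. Assumed: a 14/15 split of the 29 clusters, two-sided tests and, at first, equal cluster sizes.

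**Formulas.**
- Design effect: DE = 1 + (m − 1) × ICC
- Standard error: SE = SD × √[DE × (1/n₁ + 1/n₂)]
- Detectable difference: (z for alpha + z for power) × SE. The multiplier is 2.8016 for 80% power at 0.05 and 3.8574 for 90% power at 0.01.
- Power: Φ(difference/SE − critical z)

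**Planned design.** DE = 1 + 19 × 0.37 = 8.03. SE = 1.25 × √[8.03 × (1/340 + 1/340)] = 0.2717. Power for 0.5 = Φ(0.5/0.2717 − 1.96) = 0.452.

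**Recruited design.** DE = 1 + 17.41 × 0.37 = 7.44. SE = 0.2953. Power for 0.57 = Φ(0.57/0.2953 − 1.96) = 0.488.

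| Design | Alpha | Difference stated | Power stated | Power from inputs | Detectable difference from inputs |
|---|---|---|---|---|---|
| 34 clusters | 0.05 | 0.5 | 80% | 45% | 0.76 |
| 34 clusters | 0.01 | 0.686 | 90% | 48% | 1.05 |
| 29 clusters | 0.05 | 0.57 | 80% | 49% | 0.83 |
| 29 clusters | 0.01 | 0.78 | 90% | 53% | 1.14 |

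With t quantiles (32 and 27 df) the 0.05 rows fall to 43% and 46%. If recruited cluster sizes vary with an assumed coefficient of variation (CV) of 0.3 to 0.5, the 0.83 becomes 0.86 to 0.92.

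**Could more patients per cluster rescue it?** No. As cluster size grows without limit, SE tends to 1.25 × √(0.37 × 2/17) = 0.261. The detectable difference is then 0.73 and power for 0.5 is 48%. At 20 per cluster, 80% power for 0.5 would need about 40 clusters per arm.

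**Other readings of the planned design, power for 0.5.**
- One-sided test: 58%.
- 34 clusters in each arm: 74%.
- 1.25 read as a variance: 54%.
- ICC of 0.037: 98%.
- ICC ignored: over 99%.
- One-sided with 34 clusters per arm: 83%, which misreads the totals and still misses 80%.

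**What would reproduce the figures.** With equal clusters, the 34-cluster line needs an ICC of about 0.13, or an SD of about 0.82, or a baseline correlation r of about 0.75 (variance reduced by 1 − r²). The 29-cluster line needs an ICC of about 0.145 or r of about 0.72. Unequal clusters can close the difference between the two lines: keeping ICC 0.37, r = 0.755 with a CV of 0.33 in the recruited clusters gives 0.499, 0.687, 0.569 and 0.783. An ICC of 0.129 with a CV of 0.34 fits equally well.

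**Power for 0.5 on the protocol's own recruited figure.** If 0.57 has 80% power, SE = 0.57/2.8016 = 0.2035. Power for 0.5 is Φ(0.5/0.2035 − 1.96) = 69%.

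**The case against.** The strongest reply is that 45% belongs to an unadjusted comparison of final values, which is not the planned analysis. The outcome is a change from baseline. The Statistical methods section plans a longitudinal mixed model adjusted for the covariates used in the constrained randomization, which include mean HbA1c. At this ICC most of the variance of the arm difference lies between clusters, and a baseline cluster mean acts on just that part: removing about 62% of the between-cluster variance would restore 80% power for 0.5. With assumed baseline correlations of 0.5, 0.6 and 0.7, planned power for 0.5 is 57%, 63% and 73%. The four stated differences are also mutually consistent in pairs (0.686/0.5 and 0.78/0.57 are both about 1.37), and one correlation with moderately unequal clusters reproduces all four closely. One coherent calculation with an input left out of a condensed article is therefore plausible.

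Much of this stands. The real power under the planned analysis cannot be determined from the article, and the slight mismatch between the two lines is no evidence of incoherence once cluster sizes may vary. It does not remove the defect. The paragraph attributes its results to the inputs it prints, and those inputs do not produce them. Each rescue needs a value the text does not give, or an ICC other than the one it gives. The data cannot show which applies, because a correlation of about 0.75 and an ICC of about 0.13 fit equally well. This is not a detail left to another document, since inputs and results stand together and disagree.

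**Conclusion.** The concern holds. On the printed inputs the power claims are overstated by 35 percentage points for the planned design at the 0.05 level (45% against 80%) and by 31 points for the recruited design (49% against 80%). The stated detectable differences of 0.5 and 0.57 should be 0.76 and 0.83. These values assume two-sided tests, equal clusters, a 14/15 split and no gain from baseline adjustment; t quantiles and unequal clusters make them worse, and baseline adjustment makes them better.

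On the same unadjusted basis the recruited trial has 39% power for 0.5. Accepting the protocol's own 0.57 raises this to 69%. On either basis the recruited trial does not have 80% power for the difference it calls clinically meaningful. The paragraph should be corrected before results are interpreted.

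**What to change.** Rewrite the two power statements in one of two ways.

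1. If ICC 0.37 and SD 1.25 are right and no baseline gain was used, state 0.76 and 1.05 for 34 clusters and 0.83 and 1.14 for 29, labelled as unadjusted values.
2. If another ICC or a baseline correlation was used, print it, together with the cluster-size variation and the sidedness.

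In either case, recompute for the 29 clusters actually formed. Baseline collection is complete, so the observed SD, ICC and cluster sizes can replace the assumptions. Use the variance of the adjusted primary analysis and t quantiles, and state the assumed correlation between baseline and final HbA1c with a range, since it cannot be observed before follow-up. Then say plainly that the trial does not have 80% power for 0.5 unless the recomputation shows otherwise, and that a non-significant result will be judged by whether the confidence interval excludes 0.5.

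The cost is one rewritten paragraph and a less favourable detectable difference on the printed inputs. It needs no new patients and no change to the randomization or the analysis model.
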